## **12. Concomitant Medications**

The use of any medication will not result in discontinuation of the patient from the study unless the medication(s) will interfere with the interpretation of the results of this study or will be unsafe for the patient. All medications, whether prescription or non-prescription, taken from the day of the first treatment (Day 1) through the end of the study (Month 12 of follow up) must be recorded on the CRF.

### **13. Treatment preparation**

#### **Packaging**

The pharmacist, [name] at UPOCH will be responsible for preparing the treatment packages containing either the placebo or imiquimod cream. She will provide the study packages to the doctor/nurse who will be carrying out the trials. Each package will contain the treatment indicated in the randomization list that will be generated by [name] the unblinded statistician at McGill University. Each package will contain the treatment consisting of either placebo or imiquimod cream (40 sachets in each package) clearly labeled with the study I.D. number. Each package will be properly sealed and no evidence other than the study I.D. number will be indicated on each package.

### **14. Handling, Shipping, Storage**

#### **Investigational Supplies and Handling/Preparation**

The Aldara (Imiquimod 5% cream sachets) and the identical in appearance placebo cream will be provided by 3M Pharmaceuticals. Diagnosis and treatment supplies will be provided in kits assembled at IMTAvH-UPCH Lima site which will contain gloves, gauze, cotton, slides, scalpels, single-use syringes, needles, culture tubes, antibiotics, etc..

The Aldara and placebo creams will be shipped under refrigerated conditions and will be stored upon arrival at the site in a monitored refrigerator maintained at 2-8°C in a secure, controlled location. All investigational study supplies will be stored in a locked, safe area to prevent unauthorized access. Long term storage of Aldara and placebo will be at 2-8°C, but these can be transported and used at room temperature.

**Receipt of Supplies**

The pharmacist is responsible for making an inventory of each shipment of investigational supplies received, and writing this into an accountability form. Accurate accounting of all investigational material will be made. Unused imiquimod or placebo must be retained for drug accountability by the trial Monitor.

**15. Statistical Considerations**

The randomized clinical trial study design uses a rigorous methodology to evaluate the clinical research questions posed in this proposal. The sample size has been calculated based on estimates from previous published data results and will ensure adequate statistical power while maintaining efficiency. Minimal loss to follow-up is expected (<10%). The primary analyses will be conducted excluding patients with missing outcomes. Intention-to-treat analysis will also be performed (ie. including all patients randomized).

Descriptive statistics (means  $\pm$  standard deviation (SD), proportions and, when required, medians and interquartile ranges) will be performed to compare socio-demographic, clinical and epidemiological characteristics of patients at baseline between experimental and control groups. These characteristics include: age, sex, region of residency and education/occupation, among others. Proportions of patients cured at each of the follow up dates will be assessed. Proportions will be compared between the two groups using chi-square tests. Means derived from continuous variables will be compared using t tests or non-parametric tests, as appropriate.

Time-to-cure will be compared between the two groups using Kaplan-Meier curves and crude rates of cure will be calculated by person-years. For comparison purposes, we will assume that cure occurred at the time of the visit for cured patients. In a randomized clinical trial, we expect to find no differences in patient characteristics

between the two groups. However, when sample sizes are small, it will likely be necessary to adjust for slight imbalances in independent variables between the two groups. Cox proportional-hazard models will be constructed to determine the effect of treatment on time-to-cure, adjusting for patients' baseline characteristics. Results will be expressed in terms of hazard ratios and 95% confidence intervals. The proportional hazard assumption will be examined using graphical methods and the proportional hazard test in SAS PHGLM. Secondary analyses will be conducted in a similar manner, assuming that all those who were lost to follow-up were cured only at the end of the 12 month follow-up period.

Assuming a constant hazard ratio over time, with a sample size of 40 subjects in each of the two intervention groups (total of 80 subjects), the log-rank test for equality of survival curves will have 80% power to detect a statistically significant difference in proportions cured between the two groups based on a difference in cure proportions of at least 32% (hazard ratio of 2.6, proportion cured in the control group of 35% and proportion cured in the treated group of 67% - (less than the 72% observed at 3 months in our previous trial). If the proportion cured in the experimental group is higher than 67%, then this will increase the statistical power of the test. We believe that this will provide sufficient and compelling evidence for policy-makers.

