## **6. Randomization, blinding and assignment of treatment.**

A randomization list from 1-80 will be generated by [name] at McGill University using a ratio of 1:1 to either the pentavalent antimony plus imiquimod arm or the pentavalent antimony plus placebo arm. The list will then be provided to a pharmacist, [name] at UPOCH who will be responsible for therapy preparation. This individual will not be involved in conducting the trials and therefore cannot administer the treatment or conduct patient evaluation(s). This list will contain the study I.D. numbers (1-80) and corresponding treatment assignments and remain completely blinded to the study investigators who will be treating and evaluating the patients.

Each patient will be assigned by the study doctor a study I.D. number from the above randomized list assigned in sequential order when he/she is enrolled in the trial. The study doctor at each site will ask to the study coordinator for the study ID number. The study ID number will be provide to the study coordinator by the pharmacist. This study ID number will be entered on the CRF for that patient. The nurse will then administer the treatment as detailed in section 7. The study doctor will carry out the evaluation and the nurse, doctor, and technician will remain blinded for the treatment and evaluation period.

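### The stated 80% power counts all 80 enrolled patients as evaluable, although section 15 expects some loss and excludes missing outcomes from the primary analyses; the shortfall is modest and depends on the method

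*Protocol*

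**What the plan says.** Everything needed for this point is fixed in the protocol.

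- **Power (section 15).** "the log-rank test for equality of survival curves will have 80% power to detect a statistically significant difference", and this is "with a sample size of 40 subjects in each of the two intervention groups (total of 80 subjects"). The effect assumed is "hazard ratio of 2.6, proportion cured in the control group of 35" per cent and "proportion cured in the treated group of 67" per cent. No formula, alpha or sidedness is named, and no adjustment for loss appears.
- **Enrolment (sections 3 and 6).** The total is 80: 20 per arm in Lima and 20 per arm in Cusco. The randomization list runs from 1 to 80, "using a ratio of 1:1 to either the pentavalent antimony plus imiquimod arm or the pentavalent antimony plus placebo arm". No over-recruitment is planned.
- **Loss (section 15).** "Minimal loss to follow-up is expected (<10" per cent).
- **Handling of loss (section 15).** "The primary analyses will be conducted excluding patients with missing outcomes". An intention-to-treat analysis of all randomized patients is also planned. A secondary analysis keeps lost patients and treats them as cured only at month 12.

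**The concern.** The power statement and the primary analyses rest on different numbers of patients. The power statement uses 80. At the upper bound of the protocol's own loss estimate, the exclusion rule could leave about 72. Since enrolment is also exactly 80, the sample size itself holds nothing to absorb the difference.

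Two things are at stake. Section 15 presents the sample size as securing adequate power and offers the result as evidence for policy-makers, so the figure should describe the patients who will be analysed. The exclusion rule also selects patients on whether they completed follow-up. In a time-to-cure analysis that discards visit data which ordinary censoring would use.

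**Working it through.** **Inputs**

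| Input | Value | Source |
|---|---|---|
| Patients per arm | 40 | Protocol section 15 |
| Cured, control and treated | 35% and 67% | Protocol section 15 |
| Hazard ratio | 2.6 | Protocol section 15 |
| Loss | under 10% | Protocol section 15 |
| Alpha | 0.05 two-sided | Assumption, in line with the 95% confidence intervals in section 15 |

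**1. The hazard ratio.** Under proportional hazards, HR = ln(1 - 0.67)/ln(1 - 0.35) = ln(0.33)/ln(0.65) = 2.574. The protocol rounds this to 2.6.

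**2. Reproducing the stated 80%.** Freedman's formula is: power = Phi(sqrt(D) x (HR - 1)/(HR + 1) - 1.96), where D is the expected number of cures.

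- D = 40 x (0.35 + 0.67) = 40.8.
- Power = 80.3% with HR 2.574 and 81.0% with HR 2.6.
- In reverse, 80% power needs D = 7.849 x (3.574/1.574)^2 = 40.5 cures, so N = 2 x 40.5/1.02 = 79.4 patients.

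Other formulas do not give 80% at 40 per arm. Schoenfeld gives 85.5-86.3%, the pooled two-proportion formula 83.0%, and its continuity-corrected form 76.3%. Freedman is thus the probable source of the figure, with 80 evaluable patients.

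**3. The same calculation after exclusions.** All lost patients are assumed excluded, in equal numbers per arm.

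| Loss | Per arm | Expected cures | Freedman, HR 2.574 | Freedman, HR 2.6 | Schoenfeld, HR 2.574 |
|---|---|---|---|---|---|
| 0% | 40 | 40.8 | 80.3% | 81.0% | 85.5% |
| 5% | 38 | 38.8 | 78.3% | 79.0% | 83.7% |
| 10% | 36 | 36.7 | 76.1% | 76.8% | 81.7% |

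**4. Simulating the named test.** With exponential cure times giving 35% and 67% cured by month 12, and cures recorded at the six visits, the log-rank test has about 84% power at 40 per arm and about 80-81% at 36.

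**5. The detectable difference.** By Freedman with 36 per arm, 80% power needs 68.7% cured in the treated arm (HR 2.69). That is a difference of 68.7 - 35 = 33.7 points, against the 32 stated.

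**6. Censoring instead of excluding.** Simulation was paired, with four patients lost per arm. Censoring them at their last attended visit, rather than dropping them, raised power from 81.1% to 82.4% (a gain of 1.3 points) in one scenario and from 80.4% to 82.9% (2.5 points) in another.

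**The case against.** The strongest reply is that 76% belongs to an approximation the protocol never names. The planned test is the log-rank test. Simulated directly, it still has about 80% power with 36 per arm, because Freedman's formula is conservative here by roughly the size of the shortfall. This stands: a reader might infer that the trial's power is 76%, or that the trial is underpowered, and the documents support neither. What remains is that every method loses about four points between 80 and 72 patients. A formula that justifies 80% at 80 patients does not give 80% at 72.

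Three further points have weight.

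- The loss is stated as under 10%, so the 10% row is a bound and not an expectation.
- Loss to follow-up is not the same as a missing outcome. A patient seen cured at month 2 and lost later has an observed event. Removing all lost patients is the worst case, though the protocol does not say which of them count as missing.
- A reader might infer that the design has no reserve. That goes too far. Section 15 sets the treated proportion at 67%, below the 72% seen at three months in the earlier trial. With 35% against 72%, Freedman gives 86.6% even at 36 per arm. The margin lies in the assumed effect and not in the sample size.

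The intention-to-treat and secondary analyses do keep lost patients, but section 15 plans them in addition to the primary analyses.

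**Conclusion.** The mismatch is real and its effect is modest. The 80% describes 80 evaluable patients, whereas the primary analyses may have as few as about 72. With 10% excluded, power is about 76% by the formula that reproduces the protocol's figure, 80-81% by simulation and 82% by Schoenfeld. At 5% loss Freedman gives about 78%.

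These figures assume two-sided alpha 0.05, cure proportions of 35% and 67%, proportional hazards, equal loss in both arms and exclusion of every lost patient. They do not show that the trial is too small. They show that the stated power needs its condition attached, and that the exclusion rule gives up some information without need.

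**What to change.** 1. **Restate the power in section 15.** Say that 80% refers to 80 evaluable patients, and name the formula and alpha. Add that with 10% excluded, power for 35% against 67% is about 76-82% depending on the method, and that by Freedman 80% power then needs about 35% against 69%.
2. **Change the primary time-to-cure analysis.** Replace the exclusion of patients with missing outcomes by a log-rank and Cox analysis of all randomized patients. Count cures observed before loss, and censor the remaining lost patients at their last attended visit. This recovers about 1 to 2.5 points of power in simulation and avoids selecting patients on follow-up.

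The cost is a slightly less favourable stated power and one sentence of analysis wording. Enrolment stays at 80.

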#### **8.7 Analysis of the response to therapy at 1, 2, 3, 6, 9, 12 months of follow-up:**

Improvement: Significant reduction in the size of the lesion at the time of evaluation (Stages M1-M3) compared to baseline.

Cure: Complete re-epithelialization of the lesion without inflammation (Stage M4).

Failure: Any one of the following or combined options

Stage MO at 1 month of follow up after the treatment

Stage M1 at 3 months of follow up after the treatment

Regression of the clinical stage to a lower stage or development of a new lesion.

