## **11. Patient Removal from Study**

Patients will be free to withdraw from the study at any time, for any reason, and without prejudice to further treatment. If the treating doctor determines that the clinical situation is worsening to an extent greater than a) one would expect from the natural history of the disease, or b) the range of clinical progression seen in previous cohorts of patients with similar initial clinical findings, he/she may elect to remove the patient from the clinical trial and to initiate treatment with the best medical regimen available.

Patients may also be removed from the study by the investigators, if necessary, in the event of a severe adverse event, pregnancy, or if the patient develops a concurrent illness which would preclude continuation in the study. Patients who are withdrawn from the study due to concurrent illness will be counseled by the investigators to receive the appropriate care. Patients who are removed from the study will undergo medical evaluations and will be followed for toxicity as closely as possible. Any patient who discontinues, regardless of the reason, will not be allowed to re-enroll in this study. The CRF will include reasons for withdrawal and any necessary treatment. Adverse events will be reported by the investigators and to the Ethics committee at UPOCH and McGill University.

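### The primary analysis leaves out patients with missing outcomes, while worsening patients may be removed with only toxicity follow-up named, so non-cures can drop selectively out of the primary result

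*Protocol*

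**What the plan says.** Protocol section 15 (Statistical Considerations) fixes the primary analysis set: "The primary analyses will be conducted excluding patients with missing outcomes". It then adds: "Intention-to-treat analysis will also be performed (ie. including all patients randomized". No rule is given for scoring a missing outcome in that second analysis. For losses to follow-up, section 15 plans secondary analyses "assuming that all those who were lost to follow-up were cured only at the end of the 12 month follow-up period". Expected loss to follow-up is under 10%.

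Section 11 (Patient Removal from Study) says that if the doctor judges the course to be worse than expected, "he/she may elect to remove the patient from the clinical trial and to initiate treatment with the best medical regimen available". It also permits removal for a severe adverse event. What follows removal is described as: "Patients who are removed from the study will undergo medical evaluations and will be followed for toxicity as closely as possible". Lesion assessment for efficacy is not mentioned there.

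Section 8.7 defines failure by the stage at a visit (for example "Stage MO at 1 month of follow up after the treatment", or M1 at 3 months) or by "Regression of the clinical stage to a lower stage or development of a new lesion". Removal from the trial or a switch of treatment is not on that list. Section 9 schedules lesion assessments for all patients at months 1, 2, 3, 6, 9 and 12, but nothing says whether these continue after removal.

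**The concern.** Whether a patient stays in the primary set can depend on how that patient is doing. A patient seen at stage M4 at month 2 who then disappears has an outcome, because section 15 dates cure at the visit where it is seen. A patient still uncured at month 2 who disappears may be classed as having a missing outcome. A patient removed during the 20 treatment days reaches neither the 1-month nor the 3-month stage. Such a patient counts as a failure only if a stage regression or new lesion was recorded. Those at risk of exclusion are therefore mainly non-cures.

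Two things are at stake. Dropping non-cures raises the reported cure proportion in any arm that loses them. If the arms lose different numbers, the comparison is also distorted: it favours imiquimod if more uncured imiquimod patients drop out, and works against imiquimod if more uncured controls do. With 40 patients per arm, a few patients are enough to matter.

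**Working it through.** **Inputs from the protocol.** Section 15: 40 per group, control cure 35%, experimental cure 67%, hazard ratio 2.6, log-rank test, 80% power, loss under 10% (at most 7 of 80). Sections 3 and 9: visits at 1, 2, 3, 6, 9 and 12 months. Assumptions, because the protocol does not give them: two-sided alpha 0.05, and the split of losses between arms.

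**Step 1: the plan's own power figure.** HR = ln(1 − 0.67)/ln(1 − 0.35) = 2.57, stated as 2.6. Expected cures = 40 × (0.35 + 0.67) = 40.8. Freedman's formula, power = Φ(√40.8 × (HR − 1)/(HR + 1) − 1.96), gives 80.3% at HR 2.57 and 81.0% at HR 2.6. The stated 80% is reproduced and is not in dispute.

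**Step 2: effect on the cure proportions.** Expected cures are 0.35 × 40 = 14 and 0.67 × 40 = 26.8, a true difference of 32.0 points. Removing only non-cures leaves the numerators unchanged and shrinks the denominators:

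| Non-cures dropped (control, imiquimod) | Control | Imiquimod | Difference |
|---|---|---|---|
| 0, 0 | 14/40 = 35.0% | 26.8/40 = 67.0% | 32.0 |
| 4, 4 | 14/36 = 38.9% | 26.8/36 = 74.4% | 35.6 |
| 2, 5 | 14/38 = 36.8% | 26.8/35 = 76.6% | 39.7 |
| 7, 0 | 14/33 = 42.4% | 26.8/40 = 67.0% | 24.6 |

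The difference can move either way.

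**Step 3: false-positive rate with no true difference.** Simulated trials, 40 per arm, true cure 50% in both arms, exponential time to cure read at the six visits, log-rank test. Each uncured patient is dropped with a fixed probability, so the counts are averages out of 20 uncured per arm (2 = 10%, 5 = 25%). The last column is the rejection rate in favour of imiquimod; the nominal value is 2.5%.

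| Dropped on average (control v imiquimod) | Share of 80 | Rejection |
|---|---|---|
| 4 v 4 | 10% | about 2.5% |
| 3 v 4 | 8.75% | 3.3% |
| 2 v 5 | 8.75% | 5.9% |
| 2 v 6 | 10% | 7.4% |

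Balanced loss leaves the test intact but raises both cure rates to about 20/36 = 56%. The 4 v 4 and 2 v 6 rows total 8 of 80, just above the plan's under-10% expectation; the other two lie within it.

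As a cross-check, an exact calculation for the chi-square test on proportions cured, with fixed counts dropped at 50% true cure, gives two-sided rejection of 5.7% with none dropped, 9.1% for 2 v 5 and 17.2% for 0 v 7.

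**Step 4: power at 35% v 67%.** Same simulation. With no loss, power is about 84%; this baseline is slightly above Freedman's figure because the method differs. Losing 15% of non-cures in both arms (0.15 × 26 = 3.9 control and 0.15 × 13.2 = 2.0 imiquimod) leaves about 82%. Losing 15% in the control arm only leaves about 71%, with apparent control cure of about 39%.

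**Step 5: whether the planned secondary rule repairs it.** If the dropped patients are put back as cured at month 12, the 2 v 6 case gives about 9% rejection in favour of imiquimod, and the control-only case gives about 66% power. Neither is better than the primary analysis. No analysis in section 15 is stated to score a removed patient as not cured.

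**The case against.** The other side has real substance.

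- A reader might infer that every removed patient has no outcome and leaves the primary analysis. The protocol does not say this. A recorded stage regression or new lesion is failure under section 8.7, and lesions are assessed at the treatment visits and at follow-up. The gap concerns patients removed without such a record, for whom no scoring rule exists.
- A reader might infer that local intolerance will drive heavier loss on imiquimod. Section 10.1 says that intolerable treatment is recorded as an adverse event and the cream stopped; it does not remove the patient. Only the discretionary removal for a severe adverse event in section 11 remains as a route.
- A reader might take it as settled that a partly followed, uncured patient is dropped. Section 15 also plans Kaplan-Meier and Cox analyses, in which such a patient could be censored. The text can be read either way.
- The larger distortions need markedly unequal loss with every excluded patient uncured. No section supports a particular split, and staff who treat and evaluate are blinded apart from code-opening after a serious adverse event.
- An analysis of all randomised patients is already planned, so the excluded patients would not go unreported.

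These points limit the size and certainty of the bias. They do not change the fact that the protocol gives primary status to the set that can depend on outcome, or that the all-randomised analysis has no scoring rule.

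**Conclusion.** The point holds as a should-fix. Section 15 gives primary status to the analysis that excludes missing outcomes. Section 11 allows removal linked to poor response or harm without stating that efficacy assessment continues. Together they let non-cures leave the primary result.

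On the assumptions above (two-sided alpha 0.05, 40 per arm, all excluded patients uncured), the consequence runs from no inflation of the false-positive rate under balanced loss to about 5.9% instead of 2.5% for the 2 v 5 split, which is within the planned loss. Power falls little under equal proportional loss and to about 71% if only controls are lost. The direction cannot be predicted. A reader might conclude that the result is bound to be biased towards imiquimod, or that a tripled false-positive rate is to be expected; the documents support neither.

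**What to change.** In section 15:

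- Make the analysis of all randomised patients, as allocated, the primary one.
- Censor uncured patients who are simply lost at their last visit.
- Keep patients removed for worsening or an adverse event, or switched to other anti-leishmanial treatment, in the analysis as not cured through month 12. Censoring them at removal would not do, because that censoring is tied to poor response.
- Make the analysis excluding missing outcomes a sensitivity analysis.

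In section 11, state that the lesion assessments already scheduled for months 1 to 12 continue after removal where the patient agrees. The rule on when a patient may be removed does not need to change for this purpose.

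The cost is protocol wording and the completion of visits that are already scheduled. On the plan's own rates, 80 patients still give 80 to 81% power by Freedman's formula, so the sample size need not change. Reported cure rates may be slightly lower. Scoring removed patients as not cured is one choice of estimand, and a sensitivity analysis should vary it.

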## 3. Trial Design

A randomized, double-blind clinical trial will involve a total of 80 patients. The randomization procedure is detailed below in section 6 under Randomization, blinding and assignment of treatment. The trial will be conducted at the Instituto de Medicina Tropical Alexander von Humbolt -Universidad Peruana Cayetano Heredia (IMTA vH-UPCH) in Lima site for patients infected with *L. peruviana* and the IMTA vH-UPCH Cusco site, for patients infected with *L. braziliensis*. The groups will be assigned the following regimens: The Lima arm will include 20 experimental and 20 placebo patients. Likewise, the Cusco arm will include 20 experimental and 20 placebo patients.

Control: Standard dose of pentavalent antimony (Glucantime™ 20 mg/kg IV infusion/day for 20 days) plus placebo cream (thin layer cream applied to each lesion three times per week for 20 days).

Experimental: Standard dose of pentavalent antimony (Glucantime™ 20 mg/kg IV infusion/day for 20 days) plus standard dose of Aldara™ (5% imiquimod cream applied

to each lesion three times per week for 20 days). All patients will be subjected to follow-up clinical evaluations at 1, 2, 3, 6, 9 and 12 months after the last treatment (Day 20). The follow up evaluations will be performed by the investigation team. The endpoint for clinical cure will be complete re-epithelialization of the lesion with no sign of inflammation.

Patients will be recruited from highly endemic areas which are within one day driving from the study centers in Lima and Cusco including Ancash, Churin, Yumpe, , Sicuani, and surrounding areas. Note, that patients treated in Cusco have predominantly *L. braziliensis* infections and patients treated in Lima, Ancash, Churin and Yumpe have predominantly *L. peruviana* infections. Study teams (consisting of a UPCH trained doctors, nurses, and technicians) will carry out the treatments at IMTAvH Lima site under the supervision of [name] and at IMTAvH Cusco site under the supervision of [name]. [name] will oversee the treatments and follow-up at each center. Following the completion of therapy, the teams will then coordinate follow-up visits at 1, 2, 3, 6, 9 and 12 months. [name] will coordinate the follow up visits as he has done previously in these types of studies.

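### The time-to-cure analysis names no site or species term and justifies Cox adjustment by observed imbalance; stratifying by site and fixing prognostic covariates in advance would be a nearly free improvement

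*Protocol*

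**What the plan says.** **Design.** Protocol Section 3 assigns Lima to *L. peruviana* and Cusco to *L. braziliensis*, with equal arms at each: "The Lima arm will include 20 experimental and 20 placebo patients", and the same for Cusco. Under Personnel Responsibilities in Peru, the same section gives one reason for two units as finding out whether the treatments act alike against the two species.

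**Allocation.** Section 6 describes one list of 80, "using a ratio of 1:1 to either the pentavalent antimony plus imiquimod arm" or the placebo arm. Each patient receives "a study I.D. number from the above randomized list assigned in sequential order". No site strata are mentioned.

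**Analysis.** Section 15 compares time-to-cure between the two groups with Kaplan-Meier curves and builds Cox models adjusted for baseline characteristics that it does not list. The reason given is that with small samples "it will likely be necessary to adjust for slight imbalances in independent variables between the two groups". Age, sex, region of residency and education/occupation appear earlier in the section as examples for the descriptive baseline comparison.

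**Power.** The log-rank test is named only in the sample-size paragraph, which says that "the log-rank test for equality of survival curves will have 80% power". The inputs given there are 40 patients per arm, 80 in all, and a "hazard ratio of 2.6, proportion cured in the control group of 35% and proportion cured in the treated group of 67" per cent.

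**The concern.** Two features of Section 15 fit the design poorly.

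1. Site, which closely tracks species, is the main structural factor of the trial, but no stated analysis uses it. If cure differs between sites, a pooled log-rank test or Cox model mixes patients with different underlying cure rates. That pulls the pooled hazard ratio towards 1 and costs power. The stated aim of seeing whether the treatments work similarly in both species also has no analysis attached.

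2. Imbalance is the wrong ground for adjustment. In a randomized trial a variable that predicts cure is worth adjusting for even when the arms are balanced on it. An imbalanced variable that does not predict cure is not. Tying adjustment to what the data show also leaves the adjusted hazard ratio open to choice after the arms have been compared.

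At stake is some power in a trial of 80 patients, and a clear, single adjusted estimate.

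**Working it through.** **Step 1. Reproduce the stated power.** Inputs from Section 15: 40 per arm, cure 35% v 67%, hazard ratio 2.6. Alpha is not stated; 0.05 two-sided is assumed, in line with "Results will be expressed in terms of hazard ratios and 95% confidence intervals".

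- Hazard ratio under constant hazards: ln(1 − 0.67)/ln(1 − 0.35) = ln(0.33)/ln(0.65) = 2.57, stated as 2.6.
- Expected cures: 40 × (0.35 + 0.67) = 40.8.
- Freedman: power = Φ(√40.8 × (HR − 1)/(HR + 1) − 1.96). At HR 2.6: Φ(6.39 × 0.444 − 1.96) = Φ(0.88) = 81.0%. At HR 2.57: 80.3%.
- Schoenfeld gives 86.3% and 85.5%.

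The 80% therefore reproduces as a plain two-group log-rank calculation.

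**Step 2. Unstratified v site-stratified log-rank.** The documents give no cure rate by site, so a range was assumed around an average control cure of 35%. Simulation: 40 patients per site, within-site hazard ratio 2.6, constant hazards, cure recorded at visits at 1, 2 and 3 months, 4,000 trials per setting.

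| Control cure at the two sites | Single list: unstratified / stratified | Site-balanced allocation: unstratified / stratified |
|---|---|---|
| 35% / 35% | 85.5% / 85.0% | 85.2% / 85.0% |
| 45% / 25% | 81.6% / 84.1% | 81.7% / 84.1% |
| 55% / 15% | 67.9% / 82.3% | 70.0% / 82.0% |
| 65% / 5% (extreme) | 41.2% / 78.2% | 35.9% / 79.0% |

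A separate simulation at HR 2.57 (4,000 trials per setting) gave 68.9% / 82.0% and 70.2% / 81.6% at 55/15, and 80.7% / 82.8% and 80.6% / 83.4% at 45/25. Across both, the gain is 2 to 3 points at 45/25 and about 11 to 14 points at 55/15. Simulation error is about 0.6 to 0.8 points.

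Compare within rows, not down columns. With the within-site hazard ratio held at 2.6, average treated cure falls as the sites diverge. At 55/15 it is [(1 − 0.45^2.6) + (1 − 0.85^2.6)]/2 = (0.875 + 0.345)/2 = 61%, so part of the fall down a column is a smaller overall difference.

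**Step 3. Type I error of the unstratified test** (3,000 null trials per setting). Under the single list of Section 6: 4.7% to 5.7%. Under site-balanced allocation, as the numbers in Section 3 imply: about 5% for small site effects, but 3.2% at 55/15 and 1.5% at 65/5, that is, conservative.

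**Step 4. Allocation by site under one list.** With 40 patients per site and 40 per arm, the chance of exactly 20/20 at both sites is C(40,20)²/C(80,40) = 17.7%. The chance of a 24:16 split or worse is 11.7%.

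**Step 5. Covariate choice under no treatment effect** (600 trials, four candidate covariates, hence 2⁴ = 16 sets; error about 1 point). Adjusting only for covariates with imbalance p < 0.2: type I error 4.5% to 5.0%. Taking the most favourable of the 16 sets: 7.7% to 9.0%.

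**Step 6. What a by-site estimate can show.** Each site has 20 per arm and about 20.4 expected cures. Freedman power at HR 2.6 is Φ(√20.4 × 0.444 − 1.96) = 51.9%. A by-site result can only be descriptive.

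**The case against.** The strongest reply is that this is silence, not error. Strata and the final covariate list commonly sit in a statistical analysis plan, and the one for this trial, if it exists, is not shown. Section 15 never excludes site, region of residency is a near proxy for it, and the Cox sentence contains no rule such as a threshold or stepwise selection. That much stands: the text omits site but does not forbid it, and the imbalance sentence is a motive, not an algorithm. But the motive is stated, it is the wrong one, and a separate covariate list would not correct it.

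Four stronger readings are tempting, and the documents support none of them:

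- *The plan wastes power.* This needs a site difference in cure, and none is documented. The large gain appears only with an assumed 40-point gap in control cure.
- *The test is invalid.* Type I error stays near 5% under the single list. Mechanical adjustment for imbalance does not inflate it either. Inflation came only from picking the best of many models, which the protocol does not describe, although nothing in Section 15 rules it out.
- *The 80% is wrong.* It reproduces.
- *Age, sex, residence and education/occupation are the Cox covariates, and lesion size is left out.* They illustrate the baseline table. The list is open-ended and covers clinical characteristics, so lesion measures are unnamed, not excluded.

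It is also fair to say that site as a Cox covariate would serve about as well as site as a stratum, and that no passage shows lesion area or number to be prognostic. Choosing them is a judgement for the investigators.

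**Conclusion.** The point holds in a limited form. As written, the main time-to-cure comparison ignores the factor around which the trial is built, leaves the stated species question without an analysis, and gives imbalance in place of prognostic value as the reason to adjust. The possible cost is power: nil if the sites cure alike, 2 to 3 points at 45/25% and about 11 to 14 points at 55/15%. These figures assume a common within-site hazard ratio near 2.6, average control cure of 35%, constant hazards and two-sided alpha of 0.05. Stratifying costs about half a point at most when it is not needed (85.5% v 85.0%), which is why the change is worth making without knowing the site difference. Severity is minor to moderate.

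**What to change.** In Protocol Section 15:

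1. State that the log-rank test and Cox model are stratified by site, or that site is a covariate in the Cox model.
2. Delete the imbalance rationale. Fix the other covariates in advance on prognostic grounds from data already recorded, for example baseline lesion area (Day 1 tracing, Section 8.2), number of lesions (screening examination, Section 5) and age.
3. Report the treatment-by-site estimate with its 95% confidence interval as descriptive, to answer the question in Section 3.
4. Repeat the main analysis with PCR species (Section 5) in place of site, as a sensitivity analysis. Section 3 says only that each site's infections are predominantly of one species.
5. While editing, reconcile the single sequential list in Section 6 with the 20 + 20 per site in Section 3, since the chosen stratum should match how patients were allocated.

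Items 1 to 4 are analysis wording only and need no new data, visits or patients. Item 5 needs a decision on how the list is built, and costs little if made before enrolment starts.
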